#### Secondary outcomes related to surgical and postsurgical parameters

Patient reported outcome measures:oThe SRS-22r is a scoliosis specific questionnaire aiming to estimate quality of life in patients with scoliosis [24]. It contains 24 items divided into 5 domains covering function, pain, self-image, mental health, and satisfaction. An index value is calculated for each domain and a total index value is possible to calculate ranging from 1 (worst) to 5 (best). SRS-22r will be collected from Swespine.oEOSQ-24 is a proxy answered questionnaire and will be used in individuals up to the age of 15. It consists of 24 questions of daily function, pain, pulmonary function and mobility [25]. EOSQ-24 will be collected from Swespine.oOswestry Disability index (ODI). ODI is a back specific index measuring disability due to back pain [26]. It is the recommended instrument for studies concerning back pain. An index from 0–100 is calculated. An ODI of 0–20 indicate minimal disability, 21–40; moderate disability, 41–60; severe disability, 61–80; severely crippled, 81–100; bed-bound. ODI will be collected from Swespine.oEQ-5D 3 level is a generic quality of life instrument and consists of five areas reflecting mobility, self-care, usual activities, pain/discomfort and anxiety/depression [27]. Response alternatives range from no problems to extreme problems. An index can be calculated and depending on baseline value set used the index runs between approximately −0.5 (worst possible health) to 1.0 (best possible health). The EQ-5D-3L will be used for health economic analyses. The EQ-VAS is part of the EQ-5D and registers the patient’s self-rated health on a visual analogue scale (from 0 to 100; best). EQ-5D-3L will be collected from Swespine.Total procedure time as well as normalized to number of spinal levels from the upper to the lower instrumented vertebra.Intraoperative planning time (from start of planning in navigation software until last screw planned) (only when treated with ARSN or IRSN).Instrumentation time (total time for navigated/FH screw placement from first to last screw placement).Instrumentation time normalized to number of levels.Time for intraoperative verification imaging (CBCT and/or Fluoroscopy).Screw placement time (per screw, from owl to screw placed).Intraoperative blood loss.Intraoperative complications.Length of hospital stays.Administered doses of analgesia and types of analgesic medications required.Complications: at discharge, 30-, and 90-days.Readmissions and reasons for revision surgery: at 30-, 90-days, and 1-year.Costs per patient: at discharge, 30-, 90-days, and 1-year.

### Study follow-up

Study visits are shown in Table 1. Patients will be assessed before the surgery, during the surgery and during the inpatient stay, as well as postoperatively at 3 months, 1 year, and through the Swespine registry at 2, 5, and 10 years. There will be no additional visits for the patients involved in the study compared to the clinical routine.

**Table 1 Tab1:** Study activities

	Visit 1: Screening Initial visit	Visit 2: Inpatient stay/surgery	Visits 3 + : 3 months +
Informed consent	X		
Demography	X		
Inclusion/exclusion criteria	X		
Randomization		X	
Outcome assessments	X	X	X*

^*^Outcomes assessed at regular clinical follow-ups; complications, standing spine radiographs. SRS-22r, EOSQ-24, ODI, EQ-5D-5L questionnaires collected as per Swespine routine on web or paper (preop, 1, 2, 5 and 10 years postoperatively)

Standard preoperative investigations include a low-dose computer tomography (CT), a whole spine standing radiograph and magnetic resonance imaging (MRI) of the spine. In case of navigation an intraoperative CBCT is performed. An intraoperative CBCT verification of implant positions is always performed in all cases of navigation and free hand procedures. In the immediate postoperative period, a low-dose CT is performed, as part of routine assessment. A whole spine standing radiograph is performed at 3 months and at 1 and 2 years. Curve size, type of scoliosis and other radiological parameters will be registered.

### Sample size calculation

#### Sample size for primary objective

Based on our own and studies from others we estimate that accuracy at 1 st attempt in any of the navigated groups is p_nav_ = 91% and accuracy in the free hand group is p_control_ 84% [14, 28]. Consequently, a one-sided test can be used. With a power of 80%, alpha = 0.05, a sample size of 301 screws is obtained using sample size calculation for chi-squared test with continuity correction with equal group sizes. With a possible loss of data of 10% we aim for 332 screws in each group (rounded up to the closest integer).

With a mean of 15 screws inserted in each patient [29], about 22 patients are needed in each group. A forward calculation demonstrates that for these sample sizes, and with the same accuracy as described above, a p-value of 0.006 will be returned.

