### Study outcomes and variables

Primary and secondary study outcomes will be studied in comparisons between ARSN and free hand, IRSN and free hand, and ARSN and IRSN.

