#### Sample size for secondary objectives

Potentially the difference in intraoperative radiation could be two-fold when comparing navigated and free hand groups. The study will be sufficient to identify differences down to 20% between navigated and free hand when the navigated and free hand groups are pooled with a power of 80%, alpha = 0.05.

Minimal clinical important difference for SRS-22r is around 0.4. With a power of 80%, alpha = 0.05, a sample size of 37 patients in each group would be required to detect such a difference. Pooling data from the navigated and control groups will be done and sample size sufficient with an estimated 44 patients in the navigated and free hand groups, respectively.

Operative times will be compared between navigated and free hand groups. However, the current study sample size is underpowered to identify any differences in operating time when using our own earlier data with 403 (101) minutes and 361 (150) minutes in the navigated and free hand group respectively [14]; sample size needed would be 147 patients in each group. The data obtained in the current study may therefore only be indicative.

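### The primary sample size rests on a one-sided 5% test justified only by the expected direction, and the protocol's own figures disagree on sidedness

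*Protocol article*

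**What the plan says.** Under Sample size for primary objective, the protocol article assumes that "accuracy at 1 st attempt in any of the navigated groups is p_nav_ = 91"% and that "accuracy in the free hand group is p_control_ 84"%. The next sentence is "Consequently, a one-sided test can be used". No other reason is given. With 80% power, alpha 0.05 and a continuity-corrected chi-squared calculation with equal groups, it arrives at 301 screws per group. It continues: "With a possible loss of data of 10% we aim for 332 screws in each group". At 15 screws per patient, "about 22 patients are needed in each group". It adds that at these sizes and accuracies "a p-value of 0.006 will be returned".

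Under Sample size for secondary objectives, for operating times of 403 (101) and 361 (150) minutes, "sample size needed would be 147 patients in each group".

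The section Study outcomes and variables lists the pairwise contrasts to be made: "Primary and secondary study outcomes will be studied in comparisons between ARSN and free hand, IRSN and free hand, and ARSN and IRSN".

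The Statistical analysis section names chi-square or Fisher tests for contingency tables, and a chi-squared test with post hoc analysis when several groups are compared. It gives no sidedness and no continuity correction.

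**The concern.** Almost every superiority trial expects a direction. That expectation is the hypothesis under test and cannot also be the reason for ignoring the other tail. Navigation could turn out worse than free hand in deformed anatomy, and that result would matter. Keeping alpha at 0.05 on one side allows a 5% chance of a false claim for navigation over free hand, twice the 2.5% of a conventional two-sided test.

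The argument also cannot reach all the planned comparisons. Augmented reality against infrared navigation is a primary-outcome comparison, and the same 91% is assumed for both, so no side exists to choose.

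At stake is whether the stated 80% power describes the analysis that will be reported. A chi-square test is ordinarily two-sided. If it is run that way, the trial has less power than the protocol says.

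**Working it through.** **Inputs.** From Sample size for primary objective: p1 = 0.91, p2 = 0.84, difference d = 0.07, alpha 0.05, power 80%, continuity correction, equal groups, 10% loss. From Sample size for secondary objectives: means 403 and 361, SDs 101 and 150.

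**1. Reproducing 301.** Unpooled variance: 0.91×0.09 + 0.84×0.16 = 0.2163.

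- Uncorrected: n0 = (z_alpha + z_beta)² × 0.2163 / 0.07².
- Corrected: n = (n0/4) × [1 + √(1 + 4/(n0·d))]².

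| Test at 0.05 | n0 | n corrected | Per group |
|---|---|---|---|
| One-sided (1.645 + 0.842) | 272.9 | 300.8 | **301** |
| Two-sided (1.960 + 0.842) | 346.5 | 374.5 | **375** |

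With pooled variance under the null, the corrected sizes are 303 one-sided and 378 two-sided. So 301 is the one-sided, continuity-corrected figure, and a two-sided test needs about 25% more screws (375/301 = 1.246).

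**2. Two-sided power at the planned size.** Power = Φ[(d − 1/n − 1.96·SE0)/SE1], with SE0 = √(2×0.875×0.125/n) and SE1 = √(0.2163/n); the 1/n term is dropped for the uncorrected test. At n = 301, SE0 = 0.02696 and SE1 = 0.02681:

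- corrected: (0.07 − 0.00332 − 0.05284)/0.02681 = 0.516, power 69.7%;
- uncorrected: (0.07 − 0.05284)/0.02681 = 0.640, power 73.9%.

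| Screws per group | Corrected | Uncorrected |
|---|---|---|
| 301 | 70% | 74% |
| 332 | 74% | 78% |

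Inverting the unpooled formula of step 1 instead gives 75% rather than 74% for the corrected test at 332. These figures treat screws as independent.

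**3. The forward p-value.** At n = 332, SE0 = 0.02567.

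| Test | z | One-sided p | Two-sided p |
|---|---|---|---|
| Uncorrected | 0.07/0.02567 = 2.727 | 0.0032 | **0.0064** |
| Continuity-corrected | (0.07 − 1/332)/0.02567 = 2.610 | **0.0045** | 0.0091 |

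The printed 0.006 is the two-sided, uncorrected value. The test used for sizing gives 0.0045 at 332, and 0.0067 at 301, which would print as 0.007.

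**4. The 147 patients.** Pooled SD = √[(101² + 150²)/2] = 127.9; standardised difference = 42/127.9 = 0.328. A t-test with 80% power and alpha 0.05 needs 146.5, so **147**, two-sided, and 115.3, so 116, one-sided. The printed figure is two-sided.

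**5. The allowance for loss.** 301 × 1.10 = 331.1, rounded up to 332. To keep 301 after losing 10%, one needs 301/0.90 = 334.4, so 335. After 10% loss, 332 leaves 299, and 22 × 15 = 330 leaves 297. One-sided, corrected power is 80.0% at 301, 79.8% at 299 and 79.5% at 297.

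**The case against.** The strongest reply is that the text says only that a one-sided test can be used, and says it inside the sizing calculation. The analysis section leaves the side open, and an analysis plan that is not shown may set it. This stands in part: a reader might infer that the primary analysis has been fixed as one-sided, and the document does not go that far. What it does fix is the basis of its 80% power, together with an invalid reason for that basis.

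The p-value sentence drives neither the sample size nor any decision. That is fair; it matters mainly as evidence that the same paragraph works with two different tests.

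Some stronger readings are not supported:

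- **That 332 screws and 22 patients do not follow from the inputs.** They do: 332 is 301 × 1.10 rounded up, and 332/15 = 22.1 is about 22. Dividing by 0.90 would be the better convention, but it adds three screws and moves power by less than one percentage point.
- **That the 37 patients for SRS-22r are also two-sided.** No SD is printed. An assumed SD of 0.6 gives 37 two-sided, but an assumed SD of 0.68 gives 37 one-sided. The side cannot be determined.
- **That three comparisons imply a particular inflated family-wise error rate.** Any such figure assumes pairwise tests run without a gate. The analysis section mentions a multi-group chi-squared test with post hoc analysis and does not say whether it acts as a gate.

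**Conclusion.** The point holds in this form: the trial is sized on a one-sided 5% test whose only stated justification is the expected result. That reasoning is unsound for each navigation system against free hand and cannot apply to one system against the other. The protocol is also inconsistent, with 301 one-sided, 0.006 and 147 two-sided, and the analysis tests given no side.

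Under a two-sided 5% test, 80% power needs 375 to 378 screws per group. The planned size gives about 70% to 74% at 301 evaluable screws, or 74% to 78% if all 332 are evaluable. The lower end of each range assumes a continuity-corrected analysis and the upper end an uncorrected one. All of this takes the protocol's 91% and 84% as given and makes no allowance for clustering within patients. The loss of power is moderate; what needs correcting is the reasoning and the stated power.

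**What to change.** - State the primary comparisons as two-sided at 5%. Alternatively, use one-sided 2.5% for each navigation system against free hand, with the comparison between the two systems two-sided. Delete the sentence that derives a one-sided test from the expected rates.
- Say whether the chi-square test carries a continuity correction, and restate the power at the planned size accordingly: about 70% to 74% at 301 evaluable screws, 74% to 78% at 332, noting that this ignores clustering of screws within patients.
- Delete the p = 0.006 sentence, or replace it with the value for the test that will be used (at 332 per group, two-sided: 0.0091 corrected, 0.0064 uncorrected).
- As a minor correction, allow for loss as 301/0.90 = 335, or state that about 297 to 299 evaluable screws are expected after 10% loss.

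Restated in this way, the change needs no extra patients. The cost is a documented wording change and a less favourable stated power. No interim analysis is planned and data are analysed only after database lock, so the side should be fixed before that lock.

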#### Sample size for secondary objectives

Potentially the difference in intraoperative radiation could be two-fold when comparing navigated and free hand groups. The study will be sufficient to identify differences down to 20% between navigated and free hand when the navigated and free hand groups are pooled with a power of 80%, alpha = 0.05.

Minimal clinical important difference for SRS-22r is around 0.4. With a power of 80%, alpha = 0.05, a sample size of 37 patients in each group would be required to detect such a difference. Pooling data from the navigated and control groups will be done and sample size sufficient with an estimated 44 patients in the navigated and free hand groups, respectively.

Operative times will be compared between navigated and free hand groups. However, the current study sample size is underpowered to identify any differences in operating time when using our own earlier data with 403 (101) minutes and 361 (150) minutes in the navigated and free hand group respectively [14]; sample size needed would be 147 patients in each group. The data obtained in the current study may therefore only be indicative.

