### Free hand

After standard exposure of the region of interest of the spine screws are placed based on anatomical landmarks and feeling of intact bony canals made in the pedicle [14]. If needed, fluoroscopy is performed to check the planned screw paths. After placement of the screws, the positioning is checked with a cone beam CT (O-arm or Philips Allura). Misplaced screws may be repositioned or extracted. After screw placement, rods are placed, correction of the deformity and fusion are performed, and the wound is closed.

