#### Secondary outcomes related to radiation dose exposure

The following objectives will be measured by estimates from the CBCT systems in the operating theatres (estimated by dose area product/kerma area product, radiation time, computed tomography dose index) and dosimeters.Patient radiation exposure (ED in mSv) for the whole procedure.Patient radiation exposure (ED in mSv) for fluoroscopy.Patient radiation exposure (ED in mSv) for each CBCT.Average staff radiation exposure (in Sv) for the whole procedure.

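### The claim of 80% power for a 20% radiation difference has no variability behind it and holds only if the dose CV is at most about 33% (44 v 44) or 27% (44 v 22)

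*Protocol article*

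**What the plan says.** The Introduction of the protocol article names intraoperative radiation as one of three main study domains. The outcome list treats it as secondary, for example "Patient radiation exposure (ED in mSv) for the whole procedure".

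The section on sample size for secondary objectives first says "Potentially the difference in intraoperative radiation could be two-fold when comparing navigated and free hand groups". It then says "The study will be sufficient to identify differences down to 20% between navigated and free hand when the navigated and free hand groups are pooled". The power set for this is 80%, at alpha 0.05. No mean, SD, CV, scale or sidedness is given for dose.

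The same section puts the pooled groups, for SRS-22r, at "sample size sufficient with an estimated 44 patients in the navigated and free hand groups, respectively". The primary sample size section says "about 22 patients are needed in each group", and the design sections describe three arms, of which one is free hand.

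The only outcome given with SDs is operating time: "403 (101) minutes and 361 (150) minutes in the navigated and free hand group respectively".

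The Statistical analysis section plans Student's t-test for continuous variables in two independent groups. On imaging, the augmented-reality arm uses the Philips Allura and the infrared arm the O-arm. For free hand: "After placement of the screws, the positioning is checked with a cone beam CT (O-arm or Philips Allura").

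**The concern.** Power for a relative difference is fixed by the group sizes and the CV. The section states the power and the difference but not the CV, so the claim has no visible basis. The group sizes are also uncertain, because three arms of about 22 pool to 44 navigated and 22 free hand, not 44 and 44.

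Radiation is a main domain of the trial. A reader told that the study is sufficient down to 20% may take a non-significant result as evidence against an increase in dose of 20% to 30%. Whether the design supports that depends wholly on the missing CV.

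Each pooled group also combines doses from two imaging systems. Any dose difference between the systems enters the error term of an unadjusted comparison.

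**Working it through.** **Inputs from the protocol article.** Difference 20%, power 80%, alpha 0.05; pooled sizes 44 and 44 as stated, or 44 and 22 from three arms of about 22; operating time 403 (SD 101) and 361 (SD 150) minutes; 147 per group stated for operating time; Student's t-test.

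**Input not in the article.** The CV of dose. The values of 30% to 60% below are assumptions. CV here means a common SD divided by the mean of which the 20% is taken.

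**1. Calibrating the method on operating time.** The formula is n = (1.960 + 0.842)² × (SD₁² + SD₂²) / difference².
- Two-sided: 7.849 × (101² + 150²) / 42² = 7.849 × 32,701 / 1,764 = 145.5, so 146. With the noncentral t distribution, 146 gives 79.9% and 147 gives 80.1%, so the stated 147 is reproduced.
- One-sided, the formula gives 115, which does not match.

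The section therefore appears to use two-sided t-tests, and the same method is used below.

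**2. The CV that the radiation claim needs.** By the normal approximation, the largest CV is 0.20 / [2.802 × √(1/n₁ + 1/n₂)].
- 44 v 44: 0.20 / (2.802 × 0.2132) = 33.5%; noncentral t gives 33.1%.
- 44 v 22: 0.20 / (2.802 × 0.2611) = 27.3%; noncentral t gives 26.9%.
- One-sided, the normal approximation would allow only 37.7% and 30.8%.

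**3. Power for a 20% difference, and the difference detectable with 80% power, over assumed CVs (noncentral t, two-sided).**

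| Assumed CV | Power, 44 v 44 | Power, 44 v 22 | Detectable, 44 v 44 | Detectable, 44 v 22 |
|---|---|---|---|---|
| 30% | 87% | 71% | 18% | 22% |
| 40% | 64% | 47% | 24% | 30% |
| 50% | 46% | 33% | 30% | 37% |
| 60% | 34% | 24% | 36% | 45% |

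For a two-fold difference (100% of the free-hand mean) at a CV of 50%, power exceeds 99.9% at either split.

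**4. Operating time as an illustrative proxy.** The pooled SD is √(32,701 / 2) = 127.9 minutes. The protocol does not say of which mean the 20% is taken, so three bases are shown.

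| Base mean | 44 v 44 | 44 v 22, equal variances | 44 v 22, unequal variances |
|---|---|---|---|
| 361 (free hand) | 74% | 57% | 52% |
| 382 (midpoint) | 79% | 62% | 57% |
| 403 (navigated) | 83% | 66% | 61% |

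The formula in step 1 needs 50, 44 and 40 patients per group for these three bases.

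**5. Mixing imaging systems.** If two systems are used in equal numbers and their mean doses have ratio r, the mixture adds a CV of (r − 1)/(r + 1): 20% at r = 1.5 and 33% at r = 2. With r = 2 and a within-system CV of 25% (both assumed), the total CV is √(0.333² + 0.25²) = 42%, and power at 44 v 44 is about 60%. With the between-system part removed, a CV of 25% gives about 96%.

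**The case against.** The strongest reply is that nothing here shows the 80% to be wrong. A reader might infer from operating time that the protocol's own data put the power well below 80%. They do not. At the stated 44 v 44 that spread gives 74% to 83%, depending on the base mean, which is borderline and compatible with the claim. Lower figures need the 44 v 22 reading. The secondary sample size section states 44 v 44, and 1:1 randomisation stratified by theatre could produce it through a navigated v free-hand split in each theatre. The protocol also never links the spread of operating time to that of dose. All of this stands, so the proxy is no proof of a shortfall.

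A reader might also infer that mixing imaging systems uses up the whole allowance for spread. That rests on an assumed dose ratio. The two-fold figure in the protocol compares navigated with free hand, not one system with the other.

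Further, dose is a secondary outcome, and the Limitations section concedes that the sample is too small for full interpretation of secondary outcomes. The protocol nowhere says that a non-significant radiation result would exclude differences above 20%. This limits the harm.

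What the reply does not answer is that the article itself asserts a power figure. For operating time it gives the means and SDs behind its number. For radiation it gives only the conclusion, and the general caveat in Limitations does not correct a specific statement of sufficiency.

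**Conclusion.** The point holds as an unsupported power claim, not as a demonstrated arithmetic error. Two-sided at alpha 0.05, 80% power for a 20% difference requires a dose CV of at most about 33% at 44 v 44 or about 27% at 44 v 22, and the article gives no evidence on either. At assumed CVs of 40% and 50%, power would be 64% and 46%, or 47% and 33%.

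The documents do not support the stronger conclusion that the true power is known to be below 80%. That would need a CV for dose, which they do not contain. The operating-time proxy is borderline at 44 v 44 and falls short (about 52% to 66%) only at 44 v 22. The possible two-fold difference stays detectable at the CVs considered, so only the 20% figure is affected. The results assume a common SD across the pooled groups, except where unequal variances are stated, and a t-test on the untransformed dose.

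**What to change.** 1. Reconcile the pooled group sizes: 44 v 44, as in the secondary sample size section, or 44 v 22, as three arms of about 22 imply. Then restate the radiation sentence with the assumed CV, its source, and the difference detectable with 80% power. For assumed CVs of 40% and 50% this is about 24% and 30% at 44 v 44, or about 30% and 37% at 44 v 22.

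2. Analyse log dose in a regression with treatment group and operating theatre, and optionally number of instrumented levels. Report a dose ratio with 95% confidence interval in place of an unadjusted t-test on pooled groups. Theatre is already the randomisation stratum and, because the two navigation systems stand in different theatres, should track the imaging system. Between-system dose differences then leave the error term, provided that each theatre contributes both navigated and free-hand patients. The interval also shows directly which differences a non-significant result leaves open.

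The cost is one reworded sentence and one model on data already to be collected. The stated detectable difference may become less favourable. No extra patients are needed.

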**Fig. 1 Fig1:**
[figure not shown]
Flowchart describing the study design

Study arms:Navigation group 1: Augmented reality surgical navigation (ARSN)Navigation group 2: Infrared surgical navigation (IRSN)Control group: Free hand (FH)

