### Statistical analysis

In order to evaluate hypotheses of variables in contingency tables, the Chi-square or Fisher's Exact Tests will be used as appropriate. In order to test differences in continuous variables measured on at least interval scale between two independent groups the Student’s t-test for uncorrelated means will be used. The non-parametrical Mann–Whitney test will be used to test ordinal data. Regression analysis will be used to evaluate the dependency between variables and the Pearson correlation coefficient will be used in order to test independence between variables. In addition to that descriptive statistics will be used to characterize the data; means and 95% confidence intervals will be used for parametric data, medians and interquartile ranges for non-parametric data, and number (proportions) for categorical data. In case of multiple groups comparison. ANOVA, Kruskal–Wallis, and Chi-squared tests will be used respectively, along with post hoc analysis.

Protocol deviations will be recorded transparently. However, data from the different groups will be compared based on the'intention to treat'principle. An intention to treat (ITT) analysis means that all patients, regardless of treatment change, loss to follow-up or drop-out, remain in the analysis of the group to which they were randomized.

Statistical expertise will perform the statistical analysis.

Patient reported outcome measures consisting of ordinal scales for the different indices, will be compared using the Mann–Whitney test.

Data on total time on sick leave as well as the diagnosis used for sick leave will be collected.

Data on analgesic and antibiotic use will be collected from hospital files. Since different opioids may be used, conversion to morphine equivalents may be done. Data on other analgesics will be collected. Data on costs for the prescribed pharmaceuticals will be collected. Total amount of collected opioids (continuous data consisting of morphine equivalents) will be compared with the Student’s t-test or the Mann–Whitney test, depending on distribution.

Adverse events will be collected during the follow-up and classified as minor or major [30]. Data will be analyzed as dichotomous variables with Chi-square or Fisher tests.

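### The SRS-22r size rests on 44 free-hand patients that the text never reconciles with three groups of about 22, and the planned patient-reported outcome test makes no use of the preoperative score

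*Protocol article*

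**What the plan says.** All references are to the protocol article.

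- **Number of arms.** Overview of study design describes a three-arm trial. The list of arms under Fig. 1 gives ARSN, IRSN and a single control: "Control group: Free hand (FH").
- **Group size.** Sample size for primary objective concludes that "about 22 patients are needed in each group".
- **SRS-22r.** Sample size for secondary objectives states: "Minimal clinical important difference for SRS-22r is around 0.4". At 80% power and alpha 0.05, "a sample size of 37 patients in each group would be required". After pooling both the navigated and the control data, it calls the "sample size sufficient with an estimated 44 patients in the navigated and free hand groups, respectively". It gives neither an SD nor the sidedness.
- **Radiation.** The same section says differences down to 20% can be found "when the navigated and free hand groups are pooled with a power of 80%, alpha = 0.05".
- **Allocation.** Randomization and blinding sets a 1:1 ratio stratified by operating theatre, because the two navigation systems are in different theatres. Subject enrollment closes inclusion once the two intervention arms are full and gives no free-hand target.
- **Analysis.** Statistical analysis states: "Patient reported outcome measures consisting of ordinal scales for the different indices, will be compared using the" Mann-Whitney test. It does not mention the baseline score for these outcomes.
- **Data available.** The footnote to Table 1 (Study follow-up) shows that SRS-22r, EOSQ-24, ODI and EQ-5D are collected "preop, 1, 2, 5 and 10 years postoperatively".

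**The concern.** Pooling ARSN and IRSN doubles the navigated side from 22 to 44. It cannot double a single free-hand arm. Read with three groups of about 22, the SRS-22r statement counts 22 free-hand patients who would not exist, and the comparison would have fewer controls than the 37 the section itself requires. The 20% radiation statement relies on the same pooling. The two readings differ by 22 patients (66 or 88 in total), and it is unclear which trial the power statements describe.

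The second issue does not depend on the first. The size was set on a mean difference of 0.4, and each patient's preoperative score is collected, yet the only test named for these outcomes is a two-group rank test. In small groups this gives up precision that is already available and leaves chance baseline differences unadjusted.

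**Working it through.** **1. The group size of 22.** From Sample size for primary objective: 301 screws × 1.10 = 331.1, rounded up to 332; 332 / 15 screws per patient = 22.1. About 22 per group is reproduced.

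**2. What the text implies for the free-hand number.**

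| Reading | Support | Navigated | Free-hand | Total |
|---|---|---|---|---|
| Three equal arms | Overview of study design; Fig. 1 arm list; about 22 in each group | 44 | 22 | 66 |
| Navigation v free-hand, 1:1 in each theatre | Randomization and blinding; Subject enrollment; either CBCT system allowed under Free hand; pooling of control groups under secondary objectives | 44 | 44 | 88 |

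The visible text states neither the free-hand number nor the total.

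**3. The SD behind 37 per group.** It is not given, so 37 cannot be reproduced independently. Solving the two-sided 5% t-test for a difference of 0.4, 80% power and n = 37 gives an SD of 0.598 to 0.605; 0.60 is used below. Two-sided is an assumption. It fits the same section: the operating-time figures 403 (101) and 361 (150) give a pooled SD of √((101² + 150²)/2) = 127.9, and a two-sided t-test then needs 146.5, so 147 per group, as stated.

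**4. Power for 0.4 under each reading.** SE = SD × √(1/n₁ + 1/n₂); the noncentrality is 0.4 / SE; power comes from the noncentral t distribution.

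| Navigated / free-hand | SE | 0.4 / SE | Power |
|---|---|---|---|
| 37 / 37 | 0.60 × √(2/37) = 0.1395 | 2.87 | 81% |
| 44 / 44 | 0.60 × √(2/44) = 0.1279 | 3.13 | 87% |
| 44 / 22 | 0.60 × √(1/44 + 1/22) = 0.1567 | 2.55 | 71% |

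With SD 0.61 the last two rows become 86% and 70%. At 44 / 22 the difference detectable with 80% power is 0.743 SD, and 0.743 × 0.60 = 0.45, above the stated 0.4. At 44 / 44 there is room to lose 1 − 37/44 = 16% of patients before falling to 37. If the 37 was one-sided (SD about 0.68), power is about 86% at 44 / 44 and 72% at 44 / 22, so the contrast does not depend on sidedness. A Mann-Whitney test, at an assumed relative efficiency of 0.955, costs one to two points more.

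**5. Radiation.** No coefficient of variation (CV) is stated. The effect detectable at 80% power is 0.604 SD at 44 / 44 and 0.743 SD at 44 / 22. A 20% difference therefore needs a CV of at most 0.20 / 0.604 = 33%, or 0.20 / 0.743 = 27%.

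**6. Gain from the preoperative score.** ANCOVA reduces the SD to SD × √(1 − r²), where r is the correlation of preoperative and follow-up scores. The article gives no r, so a range is assumed.

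| Assumed r | Residual SD | Power 44 / 22 | Power 44 / 44 |
|---|---|---|---|
| none used | 0.600 | 71% | 87% |
| 0.3 | 0.572 | 75% | 90% |
| 0.5 | 0.520 | 83% | 95% |
| 0.6 | 0.480 | 88% | 97% |

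At 44 / 22, power reaches 80% at r of about 0.45.

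**The case against.** The strongest reply is that 44 free-hand patients were intended. Each theatre holds one navigation system, so 1:1 allocation within a theatre is navigation against free-hand. Filling each navigation arm to 22 would then bring about 22 free-hand patients per theatre. The closing rule tied to the two intervention arms, the free-hand verification scan on either CBCT system and the mention of pooling control data all fit this. On that reading, three arms means three techniques, about 22 per group describes two comparisons of 22 with 22, and the sufficiency statement is correct. This largely stands. A reader might infer from the arm list that the trial is underpowered for SRS-22r; the document does not support that as a finding, because it does not fix the free-hand number at 22. The flowchart in Fig. 1 is also not available here and may give numbers. What remains is that the visible text has to be pieced together to reach 44, and its plainest statements point to 22.

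On the analysis, it can be said that covariates are usually left to the analysis plan, that regression is mentioned in general terms, and that change scores are not ruled out. But the article does choose a test for these outcomes, and the general regression sentence does not commit to baseline adjustment. A reader might also infer that leaving out the baseline biases the result. In a randomized comparison it does not; the cost is precision only, and its size depends on a correlation that the article does not give.

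The stakes are limited. These are secondary outcomes, and Limitations concedes that the sample is small for them. That general remark does not settle which free-hand number the specific claim of sufficiency uses.

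**Conclusion.** The point holds as an inconsistency and as an inexpensive improvement to the analysis; it does not hold as a demonstrated loss of power.

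- **Sample size.** The sections on design and primary sample size read as 44 v 22; the section on secondary objectives uses 44 v 44. If free-hand is 44, the sufficiency statement stands, with about 86–87% power. If free-hand is 22, power is about 70%, the detectable difference is about 0.45, and the radiation claim needs a smaller CV than it would at 44 v 44. These figures assume the back-solved SD of about 0.6 and a two-sided test.
- **Analysis.** Under either reading, the named test makes no stated use of the preoperative score. Over assumed correlations of 0.3 to 0.6, adjustment adds about 4 to 17 percentage points of power at 44 v 22 and 3 to 10 at 44 v 44.

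The primary endpoint is not affected by either part.

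**What to change.** 1. Reconcile Overview of study design, the arm list under Fig. 1, Subject enrollment, Randomization and blinding, and both sample size sections to one free-hand number (in total and per theatre) and one total, 66 or 88. State the SD and sidedness behind the 37.
2. If free-hand is 44, leave the sufficiency statement and say where the 44 come from. Only if free-hand is 22, restate SRS-22r power as about 70% with a detectable difference of about 0.45, and restate the 20% radiation claim for 44 v 22 with the assumed CV.
3. Make the main analysis of SRS-22r, ODI and EQ-5D index at 1 year an ANCOVA of the follow-up score, with the preoperative score and theatre as covariates, and keep the Mann-Whitney test as a sensitivity analysis. The theatre term suits the comparison of navigation with free-hand; between ARSN and IRSN, theatre coincides with technique and cannot be adjusted for.

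The cost is wording and, at most, two restated figures. No new data are needed. The small downside is that patients without a preoperative score need a simple baseline imputation.
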